#### Secondary outcome measures

The secondary outcome measures will be the amplitude (μV) and (ms) of the MEP of the mylohyoid at baseline and after electro-acupuncture or sham electro-acupuncture. The MEP will be induced by a single TMS pulse as a proxy for the TMS evoked potential in this study. The amplitude of the MEP normally changes with the varying intensity of the TMS. The amplitude of the MEP varies greatly as opposed to latency of the MEP. In practical terms, the RMT, which is the minimum intensity of the TMS from each participant, will be detected and recorded first. Then the relative stimulation intensity of the TMS will be calculated by adding or subtracting a percentage of the basic unit of RMT. Commonly, 80–120% RMT is used clinically and in research. In this study, we will use 110% RMT as a relative stimulation intensity to detect the activity of the contralateral mylohyoid swallowing motor cortex every 30 s, for three TMS pulses. In addition, the mean value, in μV and ms, of the three MEP amplitudes and latencies evoked for the contralateral mylohyoid will be recorded.

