Plasticity of the swallowing motor cortex is imperative for the recovery of patients with OD after stroke. It requires stimulation from sensory input and an undamaged map area. Studies examining the mechanisms of electro-acupuncture on OD as a sequela of stroke are difficult to perform. Therefore, lateralization of the human swallowing motor cortex excitability with electro-acupuncture in healthy subjects must be performed. The aim of this trial is to explore whether lateralization of the human swallowing motor cortex excitability in healthy subjects is present. We will then investigate the effects of electro-acupuncture on lateralization of the human swallowing motor cortex excitability by recording the resting motor threshold (RMT) and the motor evoked potential (MEP) changes in an electro-acupuncture and a sham electro-acupuncture group. We hypothesize that after administering electro-acupuncture to healthy subjects there will be a decrease in the RMT and an increase in the amplitude of the MEP in the swallowing motor cortex. This will demonstrate the activation of the swallowing motor cortex by electro-acupuncture. Results of this study will both help identify the swallowing mechanism in healthy subjects and enhance the understanding of the pathological mechanisms of OD as a sequela of stroke. It is possible the other undamaged hemisphere map area may be activated by electro-acupuncture as well, which may ultimately demonstrate mechanisms of cerebral functional reorganization and cerebral plasticity in OD as a sequela of stroke.

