### Statistical analysis

The RMT and MEP statistical analysis will be performed using the Statistical Package for Social Science (SPSS) version 17.0 (SPSS Inc., Chicago, IL, USA). Levene’s test for homogeneity of variance will be applied. If measurement data are normally distributed then the independent *t* test will be used to analyze between-group differences for each subject before and after electro-acupuncture or sham electro-acupuncture, and between the electro-acupuncture group and the sham electro-acupuncture group. Otherwise, the Wilcoxon rank sum test for a nonparametric distribution will be used. A *p* value less than or equal to 0.05 will be considered statistically significant.

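### MEP amplitude is to be tested between arms in raw microvolts, with no log scale or baseline adjustment and an unclear contrast, which can cost power for a hypothesised effect

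*Protocol article*

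**What the plan says.** The Background states the hypothesis as a fall in RMT together with "an increase in the amplitude of the MEP in the swallowing motor cortex".

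Under Secondary outcome measures the scale is raw: "The secondary outcome measures will be the amplitude (μV) and (ms) of the MEP of the mylohyoid at baseline and after electro-acupuncture". What is stored for each subject is "the mean value, in μV and ms, of the three MEP amplitudes and latencies evoked for the contralateral mylohyoid will be recorded". The same section remarks that "The amplitude of the MEP varies greatly as opposed to latency of the MEP". That remark follows directly on "The amplitude of the MEP normally changes with the varying intensity of the TMS" and leads to the choice of stimulus: "In this study, we will use 110% RMT as a relative stimulation intensity".

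Under Primary outcome measure, percent change is named, but for RMT only.

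The Statistical analysis section gives a single plan for RMT and MEP. It opens the choice of test with "If measurement data are normally distributed then the independent" t test, and falls back on the Wilcoxon rank-sum test otherwise. It mentions no transformation, ratio or covariate. The sentence that describes the comparison mixes before-and-after with between-arm language, so it can be read as a comparison of post-treatment values or of each subject's change.

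**The concern.** MEP amplitude is a positive quantity. If it is right-skewed, and if a treatment multiplies it rather than adds to it, raw microvolts are an inefficient scale. A comparison of post-treatment values leaves the collected baseline unused, so stable differences between people stay in the error term. A comparison of raw changes removes the stable level, but lets subjects with large responses dominate the variance.

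The two readings of the Statistical analysis section can also differ widely in power, and the text does not choose between them. With 20 subjects per arm, a real rise in amplitude could be missed although the data needed to see it are collected. The choice of contrast would also remain open until the data are in hand.

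**Working it through.** **No figure to reproduce.** The protocol gives no SD, effect, pre-post correlation or power for MEP amplitude. Its 20 per arm was set for RMT.

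**Inputs from the protocol.** 20 per arm (Sample size calculation); significance at 0.05 (Statistical analysis), taken as two-sided because the side is not stated.

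**Assumed inputs.** Log-normal amplitudes; a true 40% rise in one arm; between-subject log SD b = 0.7 (range 0.4 to 1.0); session log SD s = 0.3 (range 0.2 to 0.4).

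**Step 1: implied pre-post correlation.** ρ = b²/(b² + s²) = 0.49/0.58 = 0.84. Over the grid it runs from 0.16/0.32 = 0.50 to 1.00/1.04 = 0.96. Two added settings with b = 0.4 and s = 0.6 or 0.8 give 0.16/0.52 = 0.31 and 0.16/0.80 = 0.20.

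**Step 2: hand check on the log scale, centre case.** The effect is ln 1.4 = 0.336, and the standard error is SD × √(2/20) = SD × 0.316.
- Log post value, unadjusted: SD = √0.58 = 0.762, SE = 0.241, 0.336/0.241 = 1.40, power ≈ Φ(1.40 − 2.02) = 27%.
- Log ratio to baseline: SD = √(2 × 0.09) = 0.424, SE = 0.134, 0.336/0.134 = 2.51, power ≈ Φ(2.51 − 2.02) = 69%.
- Log ANCOVA: residual SD = √(0.58 × (1 − 0.845²)) = 0.407, SE = 0.129, 0.336/0.129 ≈ 2.61, power ≈ Φ(2.61 − 2.03) = 72%, before a small loss from chance baseline imbalance.

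**Step 3: simulation, needed for the raw scale, centre case.**

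| Quantity compared | t test | Rank-sum |
|---|---|---|
| Post-treatment microvolts | 22% | 25–27% |
| Raw change in microvolts | 53% | 64% |
| Log ratio to baseline | 69% | – |
| Log ANCOVA | 71% | – |

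The sample-size equivalent is ((1.96 + z_new)/(1.96 + z_old))². From 53% to 71% it is ((1.96 + 0.553)/(1.96 + 0.075))² = 1.52, or about 52% more subjects. From 64% to 71% it is ((1.96 + 0.553)/(1.96 + 0.358))² = 1.18, or about 18% more. The second comparison is the fairer one under the change reading: in this case a Shapiro-Wilk test rejected normality of raw change in at least one arm in 81% of simulated trials, so the plan's own rule would usually lead to rank-sum.

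**Step 4: how far this depends on the assumptions.** In the 11 settings with a 40% rise (correlation 0.20 to 0.96), log ANCOVA matched or beat every test the plan could mean. The gain over rank-sum on raw change was about 1 to 10 points; at b = s = 0.4, for example, power was 44% against 54%.

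A second set of runs fixed the correlation directly. For a 50% rise and log SD 0.7:

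| Correlation | Post, t | Post, rank-sum | Change, t | Change, rank-sum | Log ratio | Log ANCOVA |
|---|---|---|---|---|---|---|
| 0.2 | 36% | 41% | 27% | 28% | 28% | 43% |
| 0.5 | 36% | 41% | 37% | 41% | 43% | 53% |
| 0.8 | 36% | 41% | 69% | 77% | 80% | 83% |
| 0.9 | 35% | 40% | 91% | 96% | 98% | 98% |

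At correlation 0.2 the gap to rank-sum on change is wider (15 points here; the largest in this set was 35% against 53% at log SD 0.4 and a 30% rise). There a change score is itself the weak choice, and rank-sum on post-treatment values comes within 2 or 3 points of ANCOVA in those two cases.

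**The case against.** The strongest case against has four parts.

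**The remark on variability.** A reader might infer that the protocol itself admits a large between-subject spread that swamps the effect. It does not. The sentence contrasts amplitude with latency and sits in a discussion of stimulus intensity, which the protocol then sets relative to each subject's RMT. No between-subject SD is given. This objection stands, and the remark cannot carry a claim about size.

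**The tests.** A reader might infer that raw post-treatment values are certain to be compared, and that rank-sum does not help. Neither holds. The Statistical analysis section can be read as comparing changes, and rank-sum on change recovers 11 of the 18 points between the t test on change (53%) and log ANCOVA (71%). This stands, and it makes the likely loss modest under that reading. It does not remove the ambiguity, which in the centre case separates 22% from 53% with the same t test.

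**The log ratio.** A reader might take the log ratio to baseline as a gain without cost. With b = 0.4 and s = 0.6 (correlation 0.31) it has 24% power, against 29% for rank-sum on post-treatment values; log ANCOVA has 32%. Each recorded mean rests on only three pulses, so a low correlation cannot be excluded. Both measurements fall within one visit of 1 to 2 hours with navigated coil placement, which makes a moderate or high one plausible, but the documents do not settle it. This stands, and it is why ANCOVA is preferred.

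**The analysis plan.** A transformation or covariate for a secondary outcome may be set in an analysis plan that is not shown. That limits the weight of the point. It does not dispose of it, because the article itself states the scale and the tests, and what it states suits amplitude poorly.

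**Conclusion.** The point holds in a limited form. For MEP amplitude the protocol states raw microvolts and an unpaired test, names no log scale or baseline adjustment, and leaves the contrast unclear. If amplitudes are right-skewed and correlated within subject, this can lose power: in the centre case log ANCOVA gains some 44 to 49 points over a comparison of post-treatment values, 18 over a t test on change, and 7 over rank-sum on change.

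All of these figures are conditional on assumed spread, correlation, a proportional effect and log-normal data, none of which the documents give. They do not show that between-subject spread overwhelms the effect, nor that power is certain to be lost. Where between-subject spread is small and correlation high, the gain over a change score is close to nil. Since this is a secondary outcome, the change is worth making because it is nearly free and removes an ambiguity, not because the trial's main conclusion depends on it.

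**What to change.** In Secondary outcome measures and Statistical analysis, name one between-arm analysis for MEP amplitude: ANCOVA of log post-treatment amplitude on arm, with log baseline amplitude as covariate, for each hemisphere. Report the ratio of geometric means with its 95% CI. Keep latency in ms.

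This costs about a sentence in each section and needs no new measurements. The downside is that the effect is reported as a ratio rather than in microvolts; raw microvolt summaries by arm and time can be shown beside it.

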### Adverse events

All subjects will be assessed before and after the intervention for minor adverse events including fainting, headaches, stuck needles, bent needles, broken needles, and hematomas. If more serious adverse events occur such as hearing impairment or seizures, the trial will be immediately stopped, and necessary medical treatments will be applied. These serious adverse events will be recorded on an adverse event report form and will be monitored by the China Clinical Trial Registration Ethics Committee who may deem that the trial be discontinued.

### Data monitoring and quality control

Risks associated with this study are minimal. The principal investigator, the co-investigators, as well as the acupuncturists administering the intervention are all experienced acupuncturists who can adroitly handle an acupuncture emergency. This team will also ensure that participants consent to the study according to their own free will. The ResMan Research Manager is a public clinical trial data acquisition and management system that was established by the data monitoring committee of the Chinese Clinical Trial Registry. Data will be obtained from the case record form (CRF) and typed into the computer by two data managers. The paper and the electronic data will be checked by the two data managers. The paper data will be stored in a locked file cabinet in the principal investigator’s office at the South China Research Center for Acupuncture and Moxibustion, and the electronic data will be stored in the ResMan Research Manager. The data monitoring committee will be responsible for data monitoring to evaluate safety issues every 6 months. The committee will specifically monitor attrition rates, adverse events, and reasons for attrition and adverse events. All adverse events will be monitored quarterly, but special attention will be given to events requiring medical or surgical intervention that require hospitalization and/or prevention of death and long-term disability. Upon completion of the trial, the electronic data will be examined by the two data managers in the ResMan Research Manager and all subject data will be encoded. Furthermore, the China Clinical Trial Registration Ethics Committee will audit the study randomly as an independent body.

To maintain study quality, the researchers, including acupuncturist and research assistants, will receive specialized training with a test-retest of all trial methods, study techniques, and monitoring methods. The outcome assessment and data analysis study personnel will be blind to the study procedures.

Information on demographics, MMSE, BMI, Kubota Water Swallow Test, outcome data, and reason for attrition will be recorded in the CRF. Subjects may be excluded if they do not meet the inclusion criteria. Participation will be terminated upon subject request or withdrawal of consent. Investigators may also terminate subjects from the study to protect their safety.

### Sample size calculation

The sample size was calculated based on a pretest from a reference in this field, where the sample size was 19.36 and calculated according to the statistical formula: $$ n=\frac{2\left[{\left(\upalpha +\upbeta \right)}^2{\sigma}^2\right]}{{\left({\upmu}_1-{\upmu}_2\right)}^2} $$ where *n* was the sample size of the treatment group/control group, α is the significance level, β is the power of the test, σ is the population variance (SD) and μ_1_ − μ_2_ is the smallest effect of interest. In this study, α = 0.05, β = 0.80 (80%), σ was estimated at 13.07, and μ_1_ − μ_2_ was the RMT of the swallowing-related muscle groups (the most important index to evaluate lateralization of the human swallowing motor cortex excitability). This was the minimum clinical significance value for the RMT of the swallowing muscles that was calculated from previous trials and expert assessments, based on the primary clinical data, which was estimated at 3.57 ([name]. Effect of Electro-acupuncture at Acupoints on the Swallowing Motor Cortex in Humans, unpublished). Therefore, a sample size of 19.36 is needed in each group (electro-acupuncture and sham acupuncture). We will include 20 subjects per group condition.

Forty healthy subjects will be randomized 1:1 to the electro-acupuncture or the sham electro-acupuncture groups. Both groups will receive TMS (Magstim 200, Magstim Co. Ltd., Whitland, Wales, UK). The RMT and the MEP of the mylohyoid will be recorded using EMG (Nicolet Viking Quest, Wisconsin, USA) before and after one 15-min electro-acupuncture or sham electro-acupuncture treatment. The whole study procedure from assessing eligibility to completion of the treatment will last between 1 and 2 h.

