### Outcome measures

#### Primary outcome measure

TMS has been widely used for assessing cortical excitability. At the same time, the RMT, as a TMS measure, can be used as an indicator of cortical excitability, which is reliable in single pulse TMS measures [25, 26]. Thus, the primary outcome measure will be the percent change in the RMT of the mylohyoid at baseline and after the electro-acupuncture or sham electro-acupuncture treatment. The RMT of the mylohyoid will be delivered by a TMS pulse every 30 s bilaterally to the left and right swallowing motor cortices, respectively, for 10 pulses in the fully relaxed state. The MEP of the mylohyoid should be greater than or equal to 30 μV for at least half, or 5 of the 10 TMS pulses. The RMT is defined as the minimum intensity that is needed to elicit the MEP ≥ 30 μV in at least 50% of pulses.

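### The sample size formula uses 0.05 and 0.80 themselves instead of their normal quantiles, so 20 per group gives about 13% power on the stated inputs, not 80%

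*Protocol article*

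**What the plan says.** The Sample size calculation section prints n = 2(α+β)²σ²/(μ₁−μ₂)² for each group. It defines the terms in the bracket as probabilities: "α is the significance level" and "β is the power of the test". The values follow: "In this study, α = 0.05, β = 0.80 (80%), σ was estimated at 13.07". The difference μ₁−μ₂ "was the RMT of the swallowing-related muscle groups", estimated at 3.57 from unpublished work and expert assessment. The text adds: "This was the minimum clinical significance value for the RMT of the swallowing muscles". The result is 19.36 per group, and the trial takes 20.

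The Primary outcome measure section, in line with the abstract, states that "the primary outcome measure will be the percent change in the RMT of the mylohyoid". The Statistical analysis section plans an independent t test, or a Wilcoxon rank sum test if the data are not normal, and says that a p "value less than or equal to 0.05 will be considered statistically significant". It does not say whether the test is one-sided or two-sided.

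**The concern.** The printed formula has the familiar shape of the two-sample formula for means. In that formula the bracket holds the standard normal quantiles that correspond to the significance level and the power. Here it holds the two probabilities. For a two-sided 5% test with 80% power, the squared bracket should be about 7.85, and the protocol's is 0.85² = 0.7225. The required number is therefore understated about elevenfold.

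This paragraph is the only justification given for 40 subjects. If it stands, a null result could be read as evidence that electro-acupuncture does not alter swallowing motor cortex excitability, when the design had little chance of detecting the difference it calls important.

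There is a second, smaller problem. The sizing text speaks of RMT, gives no unit for 3.57 or 13.07 and never mentions change or percent change. The primary outcome is a percent change. Even a correct formula would not show power for that outcome until the inputs are tied to its scale.

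**Working it through.** **Inputs.** From the Sample size calculation section: difference 3.57, σ = 13.07, significance level 0.05, power 0.80, 20 per group, 1:1 allocation. A two-sided test is my assumption; the one-sided result is also given.

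**1. Reproduce the protocol's figure.** (13.07/3.57)² = 13.403. Using the probabilities themselves:

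2 × (0.05 + 0.80)² × 13.403 = 2 × 0.7225 × 13.403 = 19.37

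This matches the stated 19.36 to within 0.01, so it is how the number was obtained.

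**2. Use the quantiles.** With z(0.975) = 1.960 and z(0.80) = 0.842, the squared sum is 7.849:

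2 × 7.849 × 13.403 = 210.4, so 211 per group (422 in total, against 40)

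The t test version gives 212 per group. One-sided, the normal formula gives 166 per group.

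**3. Power at 20 per group.** The standardized difference is 3.57/13.07 = 0.27. Power is 13.4% by the noncentral t distribution and 13.6% by the normal approximation. One-sided it is about 22%.

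**4. Detectable difference.** A t test with 20 per group has 80% power for a standardized difference of 0.909, and 0.909 × 13.07 = 11.9. That is more than three times 3.57.

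**5. What the unstated scale does.** The documents give no baseline mean RMT, no before-after correlation and no SD of percent change. Power for percent change therefore cannot be computed from them; it can only be bracketed.

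- *Both figures already on the percent-change scale:* step 3 applies unchanged, about 13%.
- *Both figures in raw RMT units:* I assumed normally distributed RMT with SD 13.07 before and after treatment, a mean baseline of 50 to 70, and a shift of 3.57 in one group. I simulated the percent change and applied a two-sided t test with 20 per group.

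| Before-after correlation (assumed) | Power for percent change |
|---|---|
| 0.5 | 12–13% |
| 0.8 | 24–26% |
| 0.9 | 44–46% |
| 0.95 | 72–75% |

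Power stays below 80% at every correlation shown, including 0.95. At correlations of 0.8 and above it is higher than for raw RMT in step 3, so moving to percent change is not what lowers the power.

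**The case against.** Three points on the other side deserve weight.

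*Scale.* A reader might infer that the 80% is right for a difference in RMT and is lost only because the primary outcome is a percent change. The documents do not support that. On the stated inputs the 80% fails for RMT too. Nor do they establish that the two scales differ. The SD appears only as "σ was estimated at 13.07", with no variable or unit attached, and 3.57 is linked to the RMT without a unit. Both come from work that is not shown and could already be changes or percent changes. What stands is that the scale is not stated.

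*Meaning of σ.* The definition of σ calls it a variance and an SD in the same phrase. If 13.07 were a variance, the correct formula would give 2 × 7.849 × 13.07/3.57² = 16.1, so 17 per group, and 20 would suffice. But the protocol's formula squares σ, and 19.36 is reproduced only by squaring 13.07. As the protocol uses it, 13.07 is an SD. The sponsor should confirm this against the source data.

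*Timing and remedy.* The Trial status section puts recruitment in July 2017 to February 2018, before the article appeared in March 2019. A reader might infer that the trial must now enrol 211 per group, or must replace its primary outcome with baseline-adjusted RMT. Neither follows. The error lies in what the protocol claims for 20 per group. Changing the outcome would also rest on treating 13.07 as a raw RMT SD, which is not stated.

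**Conclusion.** The point holds as an error in the formula. With the protocol's own difference and SD, 80% power needs 211 per group, and 20 per group gives about 13% (two-sided t test). This rests on 13.07 being an SD, as the calculation uses it, and on a two-sided test; a one-sided test does not rescue the claim.

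The lack of a stated scale is a genuine but secondary gap. Power for percent change could be anywhere from about 12% to about 75% over the assumed baselines and correlations, and nothing in the protocol says where in that range the trial lies. It would be wrong to conclude that percent change is an unsuitable outcome or that it is the reason for the low power.

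**What to change.** Rewrite the sample size paragraph:

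1. Replace α and β in the formula by the normal quantiles (1.96 and 0.84 for a two-sided 5% test with 80% power), or use the t-based equivalent, and state whether the test is one-sided or two-sided.
2. Say what 3.57 and 13.07 measure, in what unit, and that 13.07 is an SD. Give the difference and SD on the percent-change scale of the primary outcome.
3. Restate the power, or the difference detectable with 80% power, for 20 per group. If the present figures prove to be percent changes, these are about 13% and 11.9 percentage points.

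The correction takes one paragraph, plus a return to the unpublished data for the percent-change mean and SD. It needs no extra subjects or measurements and no change of primary outcome. The price is that the stated power becomes much less favourable, and a null result would have to be reported as inconclusive about a difference of 3.57.

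### The 19.36 per group comes from entering 0.05 and 0.80 in place of normal quantiles; on the stated inputs 20 per group gives about 13% power, not 80%

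*Protocol article*

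**What the plan says.** The Sample size calculation section of the protocol article prints a two-group formula for a difference in means, n = 2(α+β)²σ²/(μ₁−μ₂)², and defines its terms: "α is the significance level, β is the power of the test, σ is the population variance (SD"). It then gives the values: "In this study, α = 0.05, β = 0.80 (80%), σ was estimated at 13.07". The difference is described as the minimum clinically significant value for the RMT of the swallowing muscles, "which was estimated at 3.57". The conclusion is "Therefore, a sample size of 19.36 is needed in each group (electro-acupuncture and sham acupuncture"), rounded up to 20 per group and 40 in total.

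The Statistical analysis section plans an independent t test between groups (Wilcoxon rank sum if the data are not normal). On significance it says only that a p "value less than or equal to 0.05 will be considered statistically significant", without stating one-sided or two-sided. The primary outcome is the percent change in RMT.

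**The concern.** The formula has the usual form for comparing two means, but its bracket must hold the standard normal quantiles that correspond to the significance level and the power. The section instead defines the two symbols as those probabilities, and no quantile appears anywhere in it. A bracket of 0.05 + 0.80 is far smaller than 1.960 + 0.842, and it enters squared, so the required sample size would be understated about elevenfold.

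This is the trial's only justification for its size, and it concerns the primary outcome variable. If the power is far below 80%, a non-significant result is likely even when the minimum important difference is real, and it may be read as absence of effect. If the true difference is near 3.57 or smaller, a result that does reach significance will overstate it considerably.

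**Working it through.** **Inputs, all from the Sample size calculation section:** α = 0.05; power = 0.80 (there called β); σ = 13.07; difference 3.57; 1:1 allocation; 20 per group. Sidedness is not stated, so I take two-sided as the main case and show one-sided as the range.

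**1. Reproducing 19.36.** Taking the printed formula and definitions literally:

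- 13.07² = 170.825 and 3.57² = 12.745
- n = 2 × (0.05 + 0.80)² × 170.825 / 12.745 = 2 × 0.7225 × 13.403 = 19.37

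This is the stated 19.36 apart from the last digit (19.368, truncated). Solving back from 19.36, the bracket is √(19.36 × 12.745 / (2 × 170.825)) = 0.850, which is 0.05 + 0.80. The probabilities were therefore used in the calculation itself, and this is not merely a loose description of the symbols.

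**2. The same formula with quantiles.**

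- Two-sided: z(0.975) + z(0.80) = 1.960 + 0.842 = 2.802, so n = 2 × 2.802² × 170.825 / 12.745 = 210.4, that is 211 per group. The t-based figure is 211.4, that is 212.
- One-sided: 165.7, that is 166 per group.

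**3. Power with 20 per group.** The standardised difference is 3.57 / 13.07 = 0.273. From the noncentral t distribution with 38 degrees of freedom:

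- two-sided 0.05: 13.4% (normal approximation 13.6%)
- one-sided 0.05: 21.3% (normal approximation 21.7%)

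**4. What 20 per group can detect.** For 80% power at two-sided 0.05, the t test needs a standardised difference of 0.909, that is 0.909 × 13.07 = 11.9 on the scale of 3.57. The ratio is 11.9 / 3.57 = 3.3.

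**5. Precision.** The standard error of the group difference is 13.07 × √(2/20) = 4.13. The 95% interval is ± 2.024 × 4.13 = ± 8.4. With an observed SD of 13.07, a difference must exceed 8.4 to be significant, which is 8.4 / 3.57 = 2.3 times the stated minimum.

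**6. The variance label.** If 13.07 were a variance, the SD would be √13.07 = 3.62. The literal substitution would then give 2 × 0.7225 × 13.07 / 12.745 = 1.5. The correct quantiles would give 2 × 2.802² × 13.07 / 12.745 = 16.1, and 20 per group would have 86% power by the t test. Neither 1.5 nor 16.1 is 19.36: the section's own arithmetic squares 13.07 and so uses it as an SD.

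**The case against.** The strongest objection is that 13% is the trial's power only if 13.07 is the SD of the quantity that will be analysed. The section does not say what 13.07 measures, and its source is unpublished. The primary outcome is a percent change, whereas 3.57 is described as a value for the RMT. If 13.07 is the SD of a single RMT measurement and the analysis uses simple change, the SD of the change is 13.07 × √(2(1−ρ)). The documents give no correlation ρ. For assumed values, two-sided t-test power at 20 per group is 13% at ρ = 0.5, 19% at 0.7, 47% at 0.9 and 76% at 0.95. This part stands: the actual power is unknown, and about 13% is the power on the stated inputs. It does not rescue the claim, because even 0.95 falls short of 80% and nothing in the calculation invokes such a correlation.

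Three further points can be made.

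- **Direction.** The hypothesis in the Background is directional (RMT falls), so a one-sided test might be meant. That raises power only to 21%.
- **Variance reading.** If 13.07 is really a variance, 20 per group would be adequate. The label "σ is the population variance (SD") leaves that open as a fact about the source data, but the printed formula and its result would still be wrong.
- **Setting.** A small mechanistic study in healthy volunteers may reasonably have 40 subjects. That is fair, but it is a different justification from a claim of 80% power.

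A fuller analysis plan could not repair this, because the article prints a complete calculation and that calculation is wrong.

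**Conclusion.** The concern holds. The 19.36 results from substituting probabilities for normal quantiles. With SD 13.07 and difference 3.57, 80% power at two-sided 0.05 needs 211 to 212 per group, against 20 planned, a shortfall of about 10.6-fold (212 / 20). Power at 20 per group is about 13% two-sided or 21% one-sided, and 80% power is reached only for a difference of about 11.9.

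These power figures assume that 13.07 is the SD of the analysed outcome on the same scale as 3.57, which is how the section itself uses it. The error in the calculation does not depend on that assumption: no reading that reproduces 19.36 supports 80% power, and no other part of the article corrects it. It must be fixed.

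**What to change.** - Redo the calculation with z(0.975) = 1.960 and z(0.80) = 0.842, define the symbols as quantiles, and state whether the test is one-sided or two-sided.
- State whether 13.07 is an SD or a variance, of which quantity (a single RMT, a change, or a percent change), and in which unit. Put 3.57 on the same scale as the primary outcome.
- Remove the 80% claim. If 13.07 is confirmed as the SD of the analysed outcome, say what 40 subjects deliver: about 13% power for 3.57, or 80% power for a difference of about 11.9, with a 95% interval of about ± 8.4. If it turns out to be something else, recompute on that basis and give the source of any correlation used.
- As an option, describe the between-group test as exploratory and lead the report with the estimated difference and its 95% interval. This suits the achievable precision but is a matter of choice.

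The cost is a rewritten sample size section and a less favourable stated power. No extra subjects or procedures are needed.
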